# SUMMARY

The South Africa National Department of Health (NDOH) intends to launch its newly developed National Adherence Guidelines for Chronic Diseases (HIV, TB and NCDs) throughout South Africa in the coming year. Early implementation of the “minimum package” of interventions described in the Adherence Guidelines for HIV patients will take place at 12 primary health clinics and community health centres in four provinces starting in July 2015. To maximize the learning potential of this early implementation stage, NDOH will match the intervention clinics with 12 comparison clinics and randomly allocate intervention or comparison status within the pairs of clinics. This will allow the outcomes of the interventions to be evaluated using a cluster-randomized design and generate data on the costs of implementation and the potential need for adherence support for the other diseases addressed in the guidelines (tuberculosis, hypertension, and diabetes). This protocol is for the evaluation, which will generate information on the effectiveness of minimum package interventions and help improve the design, implementation, and budgeting of the guidelines.

We will assess the effectiveness of five interventions in the minimum package: 1) Fast track initiation counseling for patients eligible for antiretroviral therapy; 2) Enhanced adherence counseling for unstable patients on HIV treatment; 3) adherence clubs for stable patients on HIV treatment; 4) decentralized medication delivery for stable patients on HIV treatment; and 5) early tracing of all patients who miss an appointment by two weeks. We will also estimate for each study site an overall “adherence guideline impact” to provide an indication of the effectiveness of the package as a whole.

In addition, we will estimate the cost of each of the interventions listed above compared to standard of care. Finally, we will describe the cascade of care for tuberculosis, hypertension, and diabetes, three other chronic diseases for which little information currently exists. To evaluate these interventions we will work with the National Department of Health (which will implement the interventions) to randomize 24 clinics in 4 provinces 1:1 to receive the interventions or continue standard of care. All evaluations will use data routinely collected by the clinics, with no study interaction with subjects. A total of 8,256 patients will be enrolled and followed for up to 20 months to estimate short- and long-term outcomes.

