- What is the effect of Enhanced Adherence Counselling on rates of being alive, in care, and virally suppressed within 3 and 12 months of intervention eligibility?

*Objective 5: Among HIV-infected patients in antiretroviral therapy programs who miss a scheduled appointment by 5 days,* ***evaluate the impact of Early Patient Tracing on retention in care****.*

Research questions:

- What is the effect of Early Patient Tracing on rates of returning to care by 3 and 12 months of tracing?
- What is the effect of Early Patient Tracing on rates of remaining in care by 12 months of tracing?

*Objective 6: For each clinic included in the study,* ***evaluate the overall impact of the Adherence Guidelines on patient outcomes****.*

Research questions:

- What is the effect of the package of interventions on patient retention in care overall?
- What is the proportion of population in need expected to benefit from the package of interventions?

*Objective 7:* ***Estimate the incremental and total cost of each of the interventions*** *listed above compared to standard of care.*

Research questions:

- What is the average cost per patient reached with the intervention?
- What is the average cost per successful outcome achieved?

*Objective 8:* ***Describe the current status of the cascade of care and adherence to treatment for tuberculosis, hypertension, and diabete****s, for the purpose of tailoring the minimum package of interventions to these conditions in the national rollout.*

Research questions:

- What is the prevalence of previously and newly diagnosed TB, hypertension, and diabetes among the population of patients presenting for care at primary health clinics, stratified by age, sex, and HIV status where possible?
- What proportion of diagnosed cases of these conditions are initiated on guideline-compliant treatment?
- What proportion of cases have satisfactory outcomes, based on current guidelines 12 months after diagnosis?
- For each condition, what proportion of patients are lost to care or discontinue treatment during the first 12 months after diagnosis?

Note that the impacts being assessed under Objectives 1-6 are the impacts of the interventions as implemented in the early phase of the national rollout of the guidelines. As is the case with program evaluations in general, results will reflect both intervention efficacy and implementation quality, which may in turn reflect the early learning stage of national policy implementation.

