## **e. Early Tracing of Patients Lost to Follow Up**

Early tracing of patients who miss an appointment by 5 days or more seeks to identify patients who have not returned to the clinic for scheduled appointments and attempts to return them to care. This intervention requires obtaining permission from patients to contact them and maintaining up to date contact information in patient records. The goal is to reduce clinic loss to follow up and improve patient outcomes by identifying those who have missed appointments and seeking to encourage them to return to care.

| *Primary outcome:* | Proportion of patients who miss a scheduled appointment by 5 days or more who return to care within 3 months of tracing |
| --- | --- |
| *Eligibility:* | All adult patients who fail to return for a scheduled appointment within 5 to 90 days from their appointment date |
| *Sample size:* | 576 (288 per arm; 24 per cluster) |
| *Data sources:* | Tier.Net; tracing registers or logbooks; appointment books; consent forms; other registers or records that document tracing attempts and interactions with patients |

In the early implementation phase at the study clinics, the government will also test fast track/spaced appointments for patients on antiretroviral therapy. This strategy is targeted at patients who are stable on treatment as defined above and therefore does overlap with the adherence club and decentralized medication delivery populations. If fast track/spaced appointments are implemented for the same patients enrolled in the adherence clubs or receiving decentralized medication delivery in the pilot facilities, the interventions evaluated will then be “adherence clubs plus fast tracked/spaced appointments” and “decentralized medication delivery plus fast tracked/spaced appointments,” as it will not be possible to distinguish between the impacts of the two interventions.

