## **b. Inclusion and Exclusion Criteria**

For Objectives 1-5 and Objective 8, we will enroll a specific cohort of patients. These will be numbered in accordance with the objective number for Objectives 1-5; for Objective 8, the cohort will be called the “TBHD cohort”, in reference to tuberculosis, hypertension, and diabetes. This TBHD cohort will be made up of patients who have been screened for TBHD (50%) and patients who are newly diagnosed with TB, hypertension or diabetes (50%). For all cohorts, inclusion and exclusion criteria are as shown below. For Objectives 1-5, these criteria follow the December 2014 national guidelines for HIV care and ART[10] and November 2015 National Adherence Guidelines for Chronic Disease (HIV, TB and NCDs) [11].

*Cohorts 1-5 and TBHD cohort inclusion criteria*

- ≥ 18 years old
- Meet the inclusion criteria for one or more of Cohorts 1-8

*Cohorts 1-5 and TBHD cohort exclusion criteria*

- Not resident in the facility’s catchment area
- Recorded intention to transfer care to a different facility within 12 months
- Pregnant and eligible for PMTCT

*Objective 1/Cohort 1 inclusion criteria (Patients newly eligible for ART—fast track treatment initiation)*

- Determined to be eligible to start ART under prevailing national guidelines (CD4 count < 500, WHO Stage 3 or 4 condition, TB, cryptococcal meningitis)

*Objectives 2 and 3/Cohorts 2 and 3 inclusion criteria (Patients stable on ART—adherence clubs or decentralized medication delivery)*

- On same ART treatment regimen for at least 12 months
- Most recent viral load taken in past 6 months
- Two consecutive viral loads undetectable (<400 copies/ml^3^)

*Objective 4/Cohort 4 inclusion criteria (Patients on ART with poor adherence—enhanced adherence counseling)*

- On first line ART for at least 6 months
- Poor adherence as indicated by an elevated viral load (>400 copies/ml^3^)

*Objective 5/Cohort 5 inclusion criteria (Patients lost from ART programs—early patient tracing)*

- Initiated ART
- Fail to return for a scheduled appointment within 5 to 90 days from their appointment date

*Objective 8/TBHD cohort inclusion criteria (Tuberculosis, hypertension, and diabetes patients)*

- Screened for or diagnosed with for TB or hypertension within the last month, or diabetes within last 6 months

*Objective 8/TBHD cohort exclusion criteria (Tuberculosis, hypertension, and diabetes patients)*

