**Table 3. Evaluation outcomes**

| **Objective** | **Primary Outcome** | **Secondary outcomes** |
| --- | --- | --- |
| Fast track ART initiation counseling (Objective 1) | Proportion of patients who initiate ART within 30 days of becoming ART eligible (S) and the proportion of patients who are alive, in care, and virally suppressed (< 400 copies/ml^3^) within nine months of ART eligibility (L). | Proportion of patients who initiate ART within one week of becoming ART eligible  Demographic and clinical characteristics of patients who do and do not achieve primary outcomes (age, sex, baseline CD4 counts, TB diagnosis, other characteristics as allowed by data). |
| Adherence clubs (Objective 2) | Proportion of patients eligible for participation in an adherence club who receive all medications within the first four months after club eligibility (S) and the proportion virally suppressed (< 400 copies/ml^3^) at twelve months after club eligibility (L). | Proportion of patients consistently participating in club  Demographic and clinical characteristics of patients who do and do not achieve primary outcomes. |
| Decentralized medication delivery (Objective 3) | Proportion of patients eligible for decentralized medication delivery who receive all medications within the first three (S) months after delivery eligibility and viral suppression (< 400 copies/ml^3^) twelve months after delivery eligibility (L). | Proportion of patients consistently receiving medications  Demographic and clinical characteristics of patients who do and do not achieve primary outcomes. |
| Enhanced adherence counseling (Objective 4) | Proportion of patients with an elevated viral load who are alive, retained in care and resuppress their viral load (< 400copies/ml^3^) within three (S) and twelve months (L) of eligibility for enhanced adherence counseling. | Demographic and clinical characteristics of patients who do and do not achieve primary outcomes. |
| Early tracing of patients lost to follow up (Objective 5) | Proportion of patients eligible for early patient tracing who return to care within three (S) and twelve (L) months of eligibility. | Proportion of patients reached by tracers  Number of tracing attempts required; proportion of patients retained in care for at least one additional routine visit after tracing  Demographic and clinical characteristics of patients who do and do not achieve primary outcomes. |

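### Objective 5's primary outcomes are timed from tracing in two places and from eligibility in Table 3, and no tracing date is defined for comparison patients or for patients never traced

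*Protocol*

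**What the plan says.** The starting point of the Objective 5 outcome differs by section of the protocol:

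- **Section 3c, Objective 5.** The first research question asks about "rates of returning to care by 3 and 12 months of tracing". The second asks about "rates of remaining in care by 12 months of tracing". Both count from tracing.
- **Section 4e, primary outcome.** Among patients at least 5 days late for an appointment, the proportion "who return to care within 3 months of tracing". Only the 3-month outcome appears here.
- **Section 10a, Table 3.** Among patients eligible for early tracing, the proportion "who return to care within three (S) and twelve (L) months of eligibility". The short-term and long-term primary outcomes both count from eligibility.
- **Section 9c.** Enrolment in Cohorts 1-5 starts on the date eligibility is determined.

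The entry rule in section 8b is a window, not a day: "Fail to return for a scheduled appointment within 5 to 90 days from their appointment date". The trigger also varies. The Summary speaks of "early tracing of all patients who miss an appointment by two weeks", while sections 3c and 4e use 5 days.

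Under section 8a the comparison clinic in each pair continues standard of care. The introduction to section 4 accepts that some eligible patients at intervention sites may not be enrolled in the intervention.

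**The concern.** A randomised comparison of return to care needs the same time zero in both arms. A clock that starts at tracing starts at receipt of the intervention. The protocol defines no such date for comparison patients, and intervention patients who are never traced have none either. The 4e outcome is therefore undefined for part of its own denominator, and whatever is substituted for the missing date breaks comparability.

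Only Objective 5 has this problem. The section 4 outcomes for the other four interventions run from eligibility.

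The short-term outcome is the one the sample size is built on (section 10b). It also feeds Objective 6 through the short-term primary outcomes, and Objective 7 through cost per primary outcome achieved.

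**Working it through.** **Comparison of the texts.** Sections 3c and 4e say tracing; Table 3 and section 9c say eligibility. No sentence states which prevails. These are two definitions of one primary outcome, and only the eligibility version can be computed for every patient in both arms.

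**What the tracing clock would do.** The protocol gives no figure to reproduce here, so this is an illustration with no true intervention effect.

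Inputs:
- Target difference of 15 points (Table 4).
- Return of 30% at 90 days from eligibility. This is assumed; Table 4 gives 20-35% for return with no or little intervention.
- 3 months taken as 90 days (assumed).
- Comparison patients timed from eligibility, because no tracing date is defined for them (assumed).
- Every intervention patient traced at lag L days after eligibility, with L from 7 to 60 (assumed).
- Proportion still absent at day t: S(t) = 0.7^((t/90)^k). k = 1 is a constant return hazard; k = 0.7 and k = 0.5 are declining hazards (assumed).

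Two ways of applying the tracing clock in the intervention arm:
- All eligible patients counted: artefact = 1 - S(90 + L) - 0.30.
- Only those still absent at tracing counted: artefact = 1 - S(90 + L)/S(L) - 0.30.

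Worked cases at L = 60:
- All counted, k = 1: 1 - 0.7^(150/90) = 1 - 0.552 = 0.448, so +14.8 points.
- Still absent only, k = 0.5: the exponent is (150/90)^0.5 - (60/90)^0.5 = 1.291 - 0.816 = 0.4745 before rounding. Then 1 - 0.7^0.4745 = 0.156, so -14.4 points.

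Artefact in percentage points:

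| Lag (days) | All, k=1 | All, k=0.7 | All, k=0.5 | Still absent, k=1 | Still absent, k=0.7 | Still absent, k=0.5 |
|---|---|---|---|---|---|---|
| 7 | +1.9 | +1.3 | +0.9 | 0 | -2.9 | -6.3 |
| 14 | +3.8 | +2.6 | +1.8 | 0 | -4.3 | -8.4 |
| 30 | +7.8 | +5.4 | +3.8 | 0 | -6.3 | -11.4 |
| 60 | +14.8 | +10.0 | +6.9 | 0 | -8.5 | -14.4 |

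The sign depends on who is counted, and the size depends on the lag. With eligibility as the clock in both arms, the artefact is 0 at every lag. The 12-month outcome has the same defect of definition but was not quantified.

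**The case against.** The strongest reply is that the protocol already contains a common clock. Section 10a presents Table 3 as the outcomes to be measured, section 4 refers to later sections for outcome detail, and section 9c enrols at eligibility. On that reading the wording in 3c and 4e is loose shorthand and the arms never diverge. This stands in part: different clocks arise only if the tracing wording is applied. But no sentence makes Table 3 prevail, and section 4e explicitly labels its version the primary outcome.

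Four stronger readings are tempting, and the protocol does not support them:

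- **That comparison clinics do no tracing.** The protocol never says so. Section 8a notes that most clinics already give some adherence support, and Table 4 allows for little intervention as well as none. What is true is that no tracing date is defined for comparison patients.
- **That untraced patients or early returners are excluded.** The 4e denominator includes them. Their timing is undefined, which is a gap and not a stated exclusion.
- **That intervention patients enter early and comparison patients late, giving a large spurious effect.** Section 9d describes consecutive enrolment from Tier.Net of patients newly eligible since the last review, with site visits anticipated at least every 10 days. That process is described for all sites and limits such a gap. Section 4 does add, at intervention sites, eligible patients who receive the intervention. This could affect selection, but it says nothing about entry dates.
- **That a single primary outcome is affected.** Table 3 has a short-term and a long-term one.

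The mismatch in the tracing trigger is a separate inconsistency. It does not itself put the arms on different clocks.

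**Conclusion.** The contradiction is established from the text and concerns time zero for both primary outcomes of Objective 5. It should be corrected, because the section 4e version cannot be computed for all of its own denominator and would bias the randomised comparison if used.

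The size is conditional. At short lags with everyone counted the artefact is small. At a 60-day lag with a constant hazard it about equals the 15-point target. If only patients still absent are counted and the hazard declines, it can reach about the same size in the opposite direction. It could therefore create an effect or hide one. These figures rest on assumed return curves, a single lag for all intervention patients and 30% return at 90 days; the protocol gives no distribution of tracing lags.

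**What to change.** 1. In sections 3c and 4e, count time from eligibility instead of tracing, to match Table 3 and section 9c.
2. Define the eligibility date as the calendar day on which the patient first meets the missed-appointment threshold. Compute it from appointment records in the same way in both arms, not from the day staff identify or trace the patient. The 5-to-90-day window does not fix this day.
3. State that patients who return before tracing, or without it, stay in the denominator.
4. Reconcile the tracing trigger between the Summary (two weeks) and sections 3c and 4e (5 days). Which is intended is for the protocol's authors to say.

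The cost is protocol wording. Scheduled and actual visit dates and eligibility dates are already among the data fields in section 9b. The drawback is that patients who return unprompted stay in the denominator, so the baseline return proportion may be higher than planned, and the Objective 5 baseline in Table 4 should be checked against the final definition.

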# ADHERENCE STRATEGY IMPACT (OBJECTIVE 6)

To capture the effect of the Adherence Guidelines as a whole, under Objective 6 an overall “adherence strategy impact” including the effects of all interventions conducted will be estimated for each study site (cluster), to provide an indication of the effectiveness of the package as a whole. This analysis will rely on the same data collected under Objectives 1-5, but will also utilize aggregate site-level reports to apply the effects of the interventions to the total population in need presenting at the evaluation clinics per year. The estimate developed for this objective will allow comparison among intervention clinics and provide NDOH with data to refine its expectations and models for long term chronic disease care.

# COST (OBJECTIVE 7)

Objective 7 calls for estimating the cost of the five interventions implemented as part of the minimum package. We will use a mix of bottom-up and top-down methods to estimate the cost per service delivered and, where data allow, the cost per outcome achieved. The same routine patient data collected for the intervention evaluation will be used to identify and quantify resource utilization per patient in care, using methods we developed for early HIV treatment studies. Unit costs will be collected from a subset of the study clinics using invoices, prices lists, and rate scales. The average cost per service delivered, per outcome achieved, per patient served, and per facility will then be estimated. If data from Objective 6 allow, we will also estimate the cost of care for tuberculosis, hypertension, and diabetes. Data and analytic methods are described in more detail below.

# TUBERCULOSIS, HYPERTENSION, AND DIABETES (OBJECTIVE 8)

Under Objective 8 we will collect baseline data to help tailor the adherence interventions to other chronic conditions in the future. This objective will focus on drug-susceptible tuberculosis, adult Type 2 diabetes mellitus, and hypertension. Routinely collected data will be used to estimate proportions of patients diagnosed with each condition, treatment uptake, and treatment retention at the same study sites in the cluster randomized trial.

The Adherence Guidelines address tuberculosis and common non-communicable diseases, like hypertension and diabetes, as well as HIV. Unlike for HIV, where much is known about the care cascade and where the “leaks” in the cascade have been identified and estimated, little is known about the care cascade for TB and even less for diabetes and hypertension. A better evidence base about current retention in care and treatment outcomes is needed to assess the magnitude of the problem and define areas most in need of targeting for adherence support before the minimum package of adherence interventions is offered to patients in these populations.

To generate this evidence, we will use routinely collected data from the same clinics at which the HIV interventions will be evaluated. From existing medical records, we will estimate the proportions of patients presenting at the clinics who are screened for TB, hypertension, and/or diabetes and those retained in care at various steps along the diagnostic and treatment cascade, stratified where data allow by HIV status, sex, age, and/or other variables. Details on specific outcomes to be estimated, sample size, and data sources are provided in later sections of this protocol.

# STUDY SITES AND POPULATION

## **a. Selection and Randomization of Study Sites**

The evaluation will be conducted at 24 primary health care clinics (PHCs) in South Africa. Six clinics will be chosen from one district each in Gauteng, KwaZulu Natal, Limpopo, and North West Provinces. These provinces have been chosen in consultation with NDOH as they are high HIV burden provinces with high burden districts and high volume clinics. Criteria for selection of clinics are:

- *High patient volume*. Although the adherence guidelines apply to multiple conditions, the impact evaluation will focus on HIV (ART initiation, retention, and adherence). To achieve adequate enrollment within the time frame of the evaluation, only sites with >1000 current ART patients will be included. (It is likely that these will be large clinics in general and thus also have relatively high volumes of TB, diabetes, and hypertension patients for Objective 8.)

- *Not already a National Health Insurance pilot site*. The NDOH is piloting a series of interventions in selected districts in preparation for the introduction of national health insurance. These districts will be excluded as they are already providing enhanced care and therefore it would be difficult to assess the impact of the minimum package interventions.
- *Generating computerized Tier.Net data*. Some clinics continue to use only paper records to record and report on ART patients. Since the evaluation will rely heavily on patient records, it will not be practical to work at sites that have not yet implemented a computer-based system. (Note that we can work at sites that are not yet networked under Tier.Net, South Africa’s national HIV patient care database, just not at those that remain paper-based.)

- *Not participating in any other adherence-related studies or pilots*. Although most clinics will already be providing some degree of adherence support to patients, under existing guidelines, a few may also be participating in research or special programmes pertaining to adherence. We would like to avoid these so that the impacts observed can be attributed to the adherence guideline interventions.

The NDOH will develop a short list of all sites in each participating province that meet these criteria. We will then assist NDOH to select three matched pairs of clinics per province. The criteria for matching are:

- *Size*. Both clinics in each pair should have either 1000-1999; 2000-4999; or ≥5000 current ART patients.
- *Setting*. Both sites in each pair should draw from the same type of community: urban; informal settlement; or rural.
- *Location*. Pairs should be located relatively nearby one another, to facilitate data collection and increase similarity of the catchment populations.

- *HIV viral suppression*. The clinics in the pair should have ART patient viral suppression rates within 10% percent of one another (if data available).

Letters indicating Provincial and District Department of Health authorization to work at each study site have been obtained and are attached. The final number of clinics selected remains at 24 clusters.

In each pair, one clinic will randomly be assigned to receive early implementation of the minimum package of interventions, while the other will continue to provide standard of care. Randomization will be done through a random number generator in Microsoft Excel with a 1:1 ratio of allocation to intervention and control clusters.

